**Fig. 4 Fig4:**
[figure not shown]
Platform screenshot displaying personalised minute-by-minute energy expenditure data and accompanying platform features for reviewing behaviour

**Fig. 5 Fig5:**
[figure not shown]
Platform screenshot depicting weekly activity patterns expressed relative to an individual’s multidimensional profile and features for exploring the impact of any changes and action plans on their behavioural goal(s)

#### Intervention: Multidimensional individualised Physical ACTivity (Mi-PACT)

In the Mi-PACT group, feedback in the form of personalised physical activity profiles will be marketed, explained and discussed with participants in supportive one-to-one coaching sessions using the web-based platform. Participants will attend their GP practice for 5 consultations with a lifestyle coach: at baseline, and after approximately 2, 4, 8 and 12 weeks. Each participant will have access to activity monitors and the web-based platform for the duration of the 3-month intervention. Training materials for lifestyle coaches as well as hand-outs provided to study participants are available on request [40].

In the first session, participants will initially receive the same standardised messages as in the control group. The primary aim of this session is to explain the multidimensional nature of physical activity, to provide an understanding of which personalised behaviours have contributed to each dimension and to explain the options and choices that are available. A further objective is to familiarise the participant to activity self-monitoring and using the web-based platform. For this purpose, each participant will be given a Mi-PACT platform user manual and quick-start guide along with an activity monitor and Universal Serial Bus (USB) cable (for docking to their computer). Participants will have access to a personalised website account (protected by a log-in and password) and accompanying software for uploading their physical activity data. Prior to their next session, participants will be encouraged to experiment and engage in new and enjoyable activities (i.e. ‘trying different things’) while self-monitoring and exploring the functionality of the platform.

Subsequent sessions will be approximately 20–30 minutes in duration. Prior to meetings, coaches will be encouraged to log-in to the platform and review participants’ profiles as a preparatory exercise to help inform session delivery. Once it is established that the participant is confidently self-monitoring and reviewing their data, the aim of the second session is to revisit the participants’ physical activity profile and to discuss aspects of their physical activity behaviour that they would consider changing. Here, there will be a particular emphasis on identifying opportunities for achievable but sufficiently meaningful modification and specific goal setting regarding what, where and how to act. Participants who have low activity in every dimension have the most ‘choice’ and will be guided through a menu of physical activity options. Participants who score well in one or more dimensions will be supported in adding to their existing behaviour knowing that what they are doing is recognised. In terms of the tone of advice provided, coaches will attempt to use neutral language and encourage choice (e.g. using terms such as ‘you may choose to’ or ‘how would you’ rather than ‘you should’ or ‘you must’) and show empathy (e.g. ‘I appreciate why you might find this difficult’). These vocalisations will be provided in a structured manner such that goals, strategies, and implementation intentions are clear, realistic, and well-defined [10].

The primary focus of subsequent sessions will involve reviewing the impact of any changes and in supporting all efforts the participant has made to be more active, as well as recalibrating specific goals and plans within the context of the individual’s existing behaviour and lifestyle. This process will be led by the participant and will inevitably be highly individualised. At the final session, participants will be encouraged to consider their progress by using the multidimensional profile to reflect on what has been achieved and to develop a future action plan towards long-term change.

Participants will be urged to make the most of the web-based platform by wearing their physical activity monitor as much as possible (day and night) and to regularly upload their data and review their informational feedback over the 3-month intervention period. As the server has two portals, one for the participant and one for the research team, technical issues (e.g. with uploading data) can be identified and resolved by the research team. For participants without access to a computer or the Internet, coaches will facilitate the upload of data to the platform within session and the individual’s profile will be made available to them as a colour print-out where applicable. Participants with limited or no access to the platform outside of sessions will be provided with a diary for recording what aspects of their physical activity they have consciously changed between sessions (i.e. for self-monitoring purposes).

#### Training of the lifestyle coaches: intervention and control

We will recruit 4–6 intervention providers from the local community (including healthcare providers and other appropriate settings) with experience and qualifications as physical activity or lifestyle advisors. Intervention providers will be added to the GP’s office for the intervention period and may include registered healthcare professionals (e.g. dieticians) and/or non-registered professionals (e.g. health trainers). This mix of personnel is included in order to make the study as pragmatic and generalisable as possible to routine healthcare practice. To ensure delivery is compliant to treatment protocol, we will implement a number of strategies to maximise and monitor trial fidelity. Lifestyle coaches will participant in 2 days of training, including: (i) understanding the multidimensional nature of physical activity, (ii) familiarising with the web-based platform and self-monitoring technology, (iii) using the integrated physical activity profile for setting specific goals and forming implementation intentions, and (iv) provision of information in an autonomy-supportive manner (facilitating the participant’s satisfaction of autonomy and competence inherent within multidimensional profiling). All coaches will be given a written manual to support delivery of the intervention and will have the opportunity to practice and receive feedback on delivery style and content. The manual includes reference to general information on facilitating behaviour change adapted from the Department for Health NHS Health Trainer Handbook [41]. Whilst sessions are not specifically founded on Self-Determination Theory, they are designed to be delivered in an autonomy-supportive style. Other materials to further support delivery of and document the intervention will be produced as required.

#### Measurements

The primary outcome measure is physical activity, which will be directly assessed using physical activity monitors (see Physical Activity Assessment) for a 7-day period at all assessment points. We will use the underlying raw data for minute-by-minute physical activity energy expenditure to extract multiple physical activity characteristics and determine the change in a given (multiple) dimension(s) of physical activity behaviour. Specifically, this includes: overall energy expenditure (expressed as PAL); time engaged in moderate-to-vigorous physical activity accumulated on a minute-by-minute basis and in bouts of at least 10 minutes; time engaged in vigorous intensity activity accumulated in bouts of at least 10 minutes; and, non-sedentary time. To explore if the change in physical activity is meaningful, we will include secondary measures of weight, height, waist circumference, fat mass, lipids (total cholesterol, high-density lipoprotein and low-density lipoprotein cholesterol, and triglycerides), glucose control (insulin and glucose) and C-reactive protein. In addition, processes of change (e.g. need satisfaction and markers of internalisation), habit strength, motivation (autonomous and controlled), and indices of well-being, health status and quality of life will all be assessed. Together with physical activity data, these measures will allow us to examine whether changes in specific dimensions of physical activity are more or less important for specific outcomes (e.g. PAL, time > 3 METs). Based on previous research, small groups of 12–20 people in each physical activity category would be sufficient to determine whether a change in a particular aspect of physical activity was important for these secondary outcomes [42].

#### Anthropometry, blood pressure and body composition

Participants will be requested to remove any footwear and to wear only light clothing for anthropometric measurements. Body mass will be measured on a calibrated electronic or balance scale to the nearest 0.1 kg, where participants will be asked to stand in the centre of the platform with their weight evenly distributed on both feet. Height will be measured using a stadiometer to the nearest 0.1 cm. Participants will be requested to hang their arms freely with their heels, gluteal area and shoulders in contact with the stadiometer and with their head in the Frankfort plane (orbitale and tragion are horizontally aligned). The participant inspires for measurement, and the recorder brings down the headboard to compress the hair. From these collective measurements, BMI will be determined (kg.m^−2^). To assess waist circumference, participants will be asked to remove or lift their top to allow access to the measurement site. Otherwise, the measurement will be taken over the thinnest layer of clothing. With the participant standing with their feet together and weight evenly distributed, waist circumference will be assessed by positioning an anthropometric tape midway between the uppermost border of the iliac crest and the lower border of the costal margin, with the tape placed around the abdomen at the level of the midway point. Following a deep inhalation and a gentle expiration, the measurement is taken at the end of the expiration, with the tape snug but not compressing the skin. Three consecutive measurements will be made to the nearest 0.1 mm. Blood pressure will be assessed using a stethoscope or automated monitor after at least a 5-minute period of seated rest. With the arm supported at the level of the heart the measurement will be taken from the brachial artery on three consecutive occasions (with the lower of the last two measurements being recorded).

#### Dual energy X-ray absorptiometry

Total percentage body fat will be estimated using dual energy X-ray absorptiometry (in participants who choose to opt-in for this measure). Descriptive information for each participant including date of birth, height and weight will be entered into the software (Hologic, Bedford, UK) before they are asked to lie supine on the scanning table (Discovery, Hologic, Bedford, UK). Participants will be positioned centrally with feet equally spaced and arms with an even gap from the trunk and asked to remain as still as possible during the 7-minute scan. Following completion of the scan, whole body composition analysis will be performed with regions sectioned as recommended (Hologic, Bedford, UK). ‘Central adipose tissue’ (abdominal subcutaneous and visceral adipose tissue) will be estimated from a central region between L1–L4, which has previously been shown to correlate with measures of metabolic health [43]. Following an overnight fast, participants will be required to consume 1 pint of water on waking (to ensure adequate hydration) and to void their bladder prior to assessment. This is important to minimise variations in hydration status between individuals and because body water affects lean mass estimates [44]. In addition, participants will only wear light clothing for the analysis. Fat mass index (FMI) will be calculated using the equation:$$ FMI = \mathrm{total}\ \mathrm{fat}\ \mathrm{mass}\ \left(\mathrm{kg}\right)/\mathrm{heigh}{t}^2\left({m}^2\right) $$

with participants classified according to FMI reference ranges for obesity classification [45].

#### Blood sampling and analysis

Fasting blood tests will take place at the GP practice between 08:00 and 11:00. Participants who are not fasted on arrival will complete the venepuncture on another occasion. Blood samples will be drawn by the research or practice nurse from an antecubital vein and dispensed into vacutainer collection tubes (Becton Dickinson, Oxford, UK) containing the anticoagulants ethylenediaminetetraacetic acid or fluoride oxalate for plasma samples, and serum-separator tubes for serum samples. Blood samples will be marked with a project identifier code and participant study number before being sent to the Royal United Hospital Bath NHS Trust Clinical Pathology Laboratory. Samples will be centrifuged at ambient temperature within 6 hours of collection (3120 g for 10 minutes). Samples will be separated and analysed within 24 hours (except for insulin which was frozen at −20 °C and analysed at a later date). Serum triglycerides, total and high-density lipoprotein cholesterol, plasma glucose, and C-reactive protein will be determined using a Cobas 8000 (Roche Diagnostics Limited, Burgess Hill, UK). Low-density lipoprotein cholesterol will be calculated using the Friedewald equation [46]. Insulin analyses will be undertaken on a Roche E170 analyser (Roche Diagnostics, Mannheim, Germany). The assay employs a direct electro-chemiluminescence immunoassay utilising a mouse monoclonal antibody labelled with ruthenium and a second mouse monoclonal antibody coupled to paramagnetic particles.

#### Questionnaire and qualitative measurements

The Psychological Need Satisfaction in Exercise Scale will be used to measure perceived competence, relatedness and autonomy [47] while motivational regulations for exercise will be assessed using the BREQ-2 [48]. Leisure-time physical activity habit will be measured using a four-item automaticity subscale of the Self-Report Habit Index [49], vitality using the Subjective Vitality Scale [50] and competence using the Perceived Competence Scale [51]. In addition, subscales from the Intrinsic Motivation Inventory [52, 53] will be adapted to specifically measure the dimensions of exercise-related interest/enjoyment, effort/importance and pressure/tension. Health status and quality of life will be assessed using the SF-36 Health Survey Questionnaire [54] and the EQ-5D 3 L [55]. In addition, the Department of Health’s Life-Stage Segmentation Toolkit [56] will be used to segment participants factoring in attitudinal and psychographic data (a person’s overall approach to life, including personality traits, values and beliefs) and within the context of their social and material circumstances.

We will conduct focus groups at the end of the trial with 20–30 participants from a subset of the intervention arm to explore their experiences from participating in the trial and to seek detailed feedback for the suitability and acceptability of the intervention components. These focus groups will specifically focus on the importance of the physical activity profiles, the usefulness of the meetings, the barriers and facilitators of change, the dimensions of physical activity that participants modified and any other lifestyle behaviours influenced by participation in the trial. We will employ purposeful sampling procedures to capture diverse experiences of responders and non-responders across different physical activity dimensions.

#### Physical activity assessment

Physical activity energy expenditure will be estimated using a Bodymedia Core monitor (BodyMedia Inc., Pittsburgh, PA, USA). This is a wireless multisensor device worn over the triceps muscle that integrates accelerometry and heat-related measurements (heat flux, galvanic skin response, skin temperature and near body ambient temperature), and sex, age, height and body mass to estimate energy expenditure using proprietary algorithms (SenseWear® Pro 8.0, algorithm v5.2, BodyMedia Inc., Pittsburgh, PA, USA). The monitor has rechargeable batteries and can be used to collect and store data for 2 weeks – with data sampled at 1-minute intervals. Previous research has shown the Bodymedia SenseWear® (BodyMedia Inc., Pittsburgh, PA, USA) device accurately measures energy expenditure relative to criterion measures [57–59] and has been increasingly used to quantify sedentary time, physical activity and energy expenditure in experimental trials [60, 61]. Participants will be required to wear the monitor for at least 6 days (including a Saturday and Sunday) to be included in the analysis [23], and will be instructed to only remove the device for showering and water-based activities. A valid day requires at least 80 % data for a given 24-hour period. As described previously, minutes spent in the distinct intensity thresholds based on metabolic equivalent cut points and multidimensional health target attainment will be calculated [6]. Data gaps will be assigned estimated basal energy expenditure [35].

#### Sham activity monitoring

A potential threat to any study that measures physical activity behaviour is confounding due to a Hawthorne effect (i.e. changes in behaviour that occur simply due to the special attention afforded by the intervention). In the past, we have deliberately avoided telling people that their physical activity is being observed (e.g. [7]) but, inevitably, this is not an option in the present study because the intervention group will become necessarily more aware of their physical activity and could potentially change their behaviour during specific outcome assessment periods (e.g. for social desirability). One approach to overcome this threat and to avoid any short-term changes in behaviour associated with physical activity outcome assessment is to extend the perceived assessment window. In order to achieve this, we will employ the use of a sham physical activity monitor worn on the wrist in the 1-month prior to follow-up measurements (in both groups). In most cases we will employ a genuine sham (i.e. an empty shell) but at least 5 % of sham monitors will be real working units (MotionWatch 8, Cambridge Neurotechnology Ltd., Cambridge, UK). The motion watch can record and store data for up to 120 days with a 1-minute sampling frequency. Participants will be told that some devices will be recording and others may not.

#### Trial fidelity

We will include a range of the strategies outlined by the National Institute of Health Behaviour Change Consortium to maximize and monitor trial fidelity across the established five domains of Study Design, Training, Delivery, Receipt, and Enactment [62]. First, we will implement standardised training of intervention providers (see Training of the lifestyle coaches: intervention and control) and will train more coaches than needed to protect against dropout. Trial fidelity will be monitored by: selective recording of consultation meetings; fidelity checklists (administered at the end of each session); and, provision of formative feedback to health trainers. Engagement of participants with the on-line platform will be assessed quantitatively by the number of occasions that participants logged in to the website. In addition, adherence to coaching sessions will be assessed by coach records of the number and format of support sessions delivered.

#### Concomitant medication and usual care

All changes in medications or new diagnoses during the course of the study will be recorded by the research nurse either in-clinic or following examination of patient records at baseline, 3 and 12 months. All relevant over-the-counter or prescription medication, the generic name of each medication, dose, frequency and history will be recorded. In addition, the research nurse will document any care participants receive in relation to supporting changes in weight or physical activity throughout the study.

### Statistics

#### Number of participants

Although an exploratory trial, it is prudent and instructive to conduct a formal sample size estimation. For this purpose, our specific outcome is mean physical activity energy expenditure (expressed as PAL). In middle-aged men [4], the standard deviation for PAL was 0.18 (we have no reason to suspect a substantially different variability in women). Our targeted effect size is a difference between intervention and control arms in the 12-month change in PAL from baseline to follow-up of 0.07. Based on our previous data [4], an increase in PAL of that magnitude would result in an increase of 10 % in the proportion meeting the minimum physical activity recommendation of a PAL of 1.6 [63], which we define as the smallest worthwhile effect [64]. With 2*P* = 0.05, 90 % power, and an assumed correlation between baseline and follow-up values of *r* = 0.7, the required sample size with an Analysis of Covariance model [65] is 108 in the intervention and 54 in the control. Allowing for 25 % loss to follow-up (attrition) results in a final target sample size of 144 in the intervention group and 72 controls. The assumed correlation between baseline and follow-up (the 12-month reliability) is a conservative estimate, as we are aware of no long-term reliability data using the best objective measures. Note that we are not, a priori, attaching primacy to PAL and we will examine multiple physical activity dimensions. PAL permits a robust sample size estimate and is clearly important.

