#### Data analysis

Analyses will be undertaken on an intention-to-treat basis. The statistical analysis plan is for a primary comparison between intervention and control arms of the 12-month change in physical activity using an analysis of covariance model [66], with baseline values as the covariate to control for chance imbalances at baseline (accounting for any unequal variance due to the unequal allocation, and including the factors used in minimisation [67]). Analysis of interaction effects involving age-group or sex will be exploratory only and used to inform sample size planning for any subsequent definitive trial or evaluation. The analysis adopts a linear mixed model to provide the mean intervention effect together with quantification (as a standard deviation) of the individual participant differences in response to the intervention (‘treatment heterogeneity’) [68]. Confidence intervals, confidence levels, and magnitude-based inferences will be used to assess the clinical significance of the effect [64, 69, 70]. The same analysis strategy is applied to each dimension of physical activity, with due account taken of multiplicity [71]. In accordance with our second objective, for body weight and composition and metabolic control outcomes we will explore – using accepted regression-modelling methods – the extent to which intervention effects are mediated by changes in physical activity dimensions. Qualitative data will be analysed using thematic analysis based on constant comparison methods [72]. Techniques to enhance dependability and trustworthiness will include the development of a detailed coding scheme and coding checking protocol, cross-tabulation, negative case analysis and respondent validation (both in situ and by inviting feedback summaries of analysed data) [73].

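### The stated 90% power is for PAL tested alone at an unadjusted 0.05; once five dimensions are adjusted for multiplicity, power for PAL falls short of 90% (75.5% if Bonferroni over five)

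*Protocol article*

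**What the plan says.** The Number of participants section of the Protocol article bases the calculation on PAL. It takes an SD from earlier data in middle-aged men ("the standard deviation for PAL was 0.18") and targets a "difference between intervention and control arms in the 12-month change in PAL from baseline to follow-up of 0.07". The remaining inputs are given as "With 2*P* = 0.05, 90 % power, and an assumed correlation between baseline and follow-up values of *r* = 0.7". The required evaluable sample "is 108 in the intervention and 54 in the control", raised to 144 and 72 for 25% attrition. The paragraph closes by declining to rank the outcomes: "Note that we are not, a priori, attaching primacy to PAL and we will examine multiple physical activity dimensions".

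The Measurements section names physical activity as the primary outcome and says the monitor data will be used to "determine the change in a given (multiple) dimension(s) of physical activity behaviour". It lists five measures: PAL, all moderate-to-vigorous minutes, moderate-to-vigorous minutes in bouts of ten minutes or longer, vigorous minutes in such bouts, and non-sedentary time. The section describing the Mi-PACT platform counts the same five.

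The Data analysis section sets out an analysis of covariance of the 12-month change and adds: "The same analysis strategy is applied to each dimension of physical activity, with due account taken of multiplicity". The method of adjustment is given there only by citation.

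**The concern.** The sizing assumes one test at 0.05. The analysis describes five outcomes, none ranked above the others, with an allowance for multiplicity. An adjusted p-value is never smaller than the raw one, so the allowance can only lower PAL's power or leave it unchanged. Testing in a fixed order with PAL first would keep PAL at 0.05, but giving PAL no primacy leaves no basis for that order.

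A reader who takes the 90% at face value will therefore expect the trial to miss a true PAL difference of 0.07 about one time in ten. The article calls a difference of that size the smallest worthwhile effect. Under the planned analysis the risk could be about one in four. That matters for reading a null result on PAL, and for planning the definitive trial that this exploratory one is meant to inform.

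**Working it through.** **Inputs** (Number of participants section unless noted): SD 0.18; target difference 0.07; r = 0.7; two-sided alpha 0.05; power 90%; evaluable 108 and 54; attrition 25%; allocation 2:1 (Randomisation/allocation section); five dimensions (Measurements section).

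**1. Reproduce the plan's figure.** 
Residual SD after baseline adjustment = 0.18 × √(1 − 0.7²) = 0.18 × √0.51 = 0.1285. 
Control n at 2:1 = 1.5 × (1.960 + 1.2816)² × 0.1285² / 0.07² = 53.15, rounded up to 54, with 108 in the intervention arm. 
After attrition: 54/0.75 = 72 and 108/0.75 = 144. All four figures match the article.

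**2. Power of the unadjusted PAL test.** 
SE = 0.1285 × √(1/108 + 1/54) = 0.02142. 
0.07/0.02142 = 3.267. 
Power = Φ(3.267 − 1.960) = 90.4% (90.1% by noncentral t).

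**3. Bonferroni over five (an assumed method).** 
Alpha = 0.05/5 = 0.01, critical value 2.576. 
Power = Φ(3.267 − 2.576) = 75.5% (74.5% by noncentral t). 
Difference detectable with 90% power = (2.576 + 1.282) × 0.02142 = 0.083. 
Half-width of the interval for PAL: 1.960 × 0.02142 = 0.042 unadjusted, 2.576 × 0.02142 = 0.055 adjusted.

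**4. Other procedures (assumed).** Five normal test statistics were simulated with a common correlation from 0 to 0.9 and 200,000 draws per case. Either PAL alone had an effect, or all five had the same standardised effect as PAL (3.267 SEs). Power for PAL:

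| Procedure | Only PAL moves | All five move equally |
|---|---|---|
| Bonferroni | about 75.5% | about 75.5% |
| Holm | about 75% to 76% | 82% to 87% |
| Hochberg | about 75% to 76% | 85% to 88% |
| Benjamini-Hochberg | about 76% | 87% to 90% |

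The highest value was 89.7% (Benjamini-Hochberg, zero correlation, all five moving).

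**5. Upper limit.** If the other four dimensions were virtually certain to be rejected, Holm, Hochberg and Benjamini-Hochberg would each in effect test PAL at 0.05, and its power would return to 90.4%. That needs clearly larger standardised effects on all four. The article gives no SD, target difference or power for any of them.

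**The case against.** The best defence is that nothing is miscalculated and nothing is hidden. The article ties the calculation to PAL for that stated purpose, says openly that PAL has no primacy, calls the trial exploratory, and nowhere claims 90% for the whole family or after adjustment. The choice of multiplicity method is properly left to the analysis plan. All of this stands, and it limits the point to clarifying a stated figure.

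Several stronger readings are tempting but not supported:

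- *The sample size is wrong.* It is not; it reproduces exactly.
- *The two statements contradict each other.* They are compatible if the 90% is read as the unadjusted PAL figure. The article does not say that it should be read that way.
- *The true power is 75.5%.* That is the Bonferroni-over-five case only. The article names neither Bonferroni nor an alpha split.
- *Success could be claimed on whichever dimension moved, or family-wise error is inflated.* Five independent unadjusted tests would give 1 − 0.95⁵ = 22.6%, but the article commits to accounting for multiplicity and states no significance rule for a positive trial. It plans confidence intervals and magnitude-based inferences.

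It can also be said that power to detect at least one dimension may exceed 90%: under Bonferroni with equal effects it is about 86% to 99.9%. That is a different quantity from the one stated, and it assumes effects on four outcomes for which the article gives no figures.

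Finally, the shortfall is sensitive to r, which the article regards as conservatively chosen while reporting no long-term reliability data. Taking other values purely as assumptions, power at alpha 0.01 would be about 83% with r = 0.75 and about 90.5% with r = 0.80. The stated figure, though, rests on r = 0.7.

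**Conclusion.** The point holds as a mismatch between the sizing and the analysis. The 90% belongs to PAL tested alone at an unadjusted two-sided 0.05, and the planned multiplicity-adjusted analysis of five dimensions does not deliver it on the article's inputs. Power for PAL is 90.4% unadjusted and 75.5% under Bonferroni over five. Step-wise and false-discovery procedures gave about 75% to 90% in the cases examined. Where in that range the trial falls depends on the method chosen and on the effects on, and correlation among, the other four dimensions, none of which is given.

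The conclusion rests on SD 0.18, r = 0.7, 108 and 54 evaluable, and all five listed measures forming one family without ranking. That last reading comes from the Measurements, Number of participants and Data analysis sections taken together; the article does not use the word co-primary. The exploratory label and the disclosed sizing basis lessen the seriousness but do not remove the mismatch.

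**What to change.** Keep the sample size and the five dimensions. In the Number of participants section, or in the analysis plan:

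1. State that the 90% refers to PAL tested on its own at 2P = 0.05, before any adjustment for the other dimensions.
2. Name the multiplicity method and the family it covers, and restate PAL power under it with 108 and 54 evaluable. If the method is Bonferroni over five, the figure is about 76%, with a detectable difference of about 0.083 at 90% power. Label it as an assumption until the method is fixed. For a step-wise or false-discovery method, give a range with the assumed effects and correlations.

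The cost is a few sentences and a less favourable power figure. Recruitment and data collection do not change.

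Naming 12-month PAL as the single primary outcome at 0.05 would also make the 90% correct, but that is a design choice for the sponsor. It would demote four dimensions in a trial whose rationale is that no single measure suffices. The Background itself notes that structured activity often changes overall energy expenditure only modestly. Enrolment had also already begun (Trial status section), so it would amend the primary outcome of a running trial.
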